### Economic analysis

A cost-utility analysis will be undertaken using a NHS and Personal Social Services (PSS) perspective. The health outcomes will be expressed in terms of quality adjusted life years (QALYs). The QALY combines length and quality of life into a single index number between 0 and 1 where 0 corresponds to a health state judged to be equivalent to death and 1 corresponds to optimal health. The SF-6D will be used to calculate QALYs. The SF-6D is composed of six multi-level dimensions which describes 18,000 health states in all. The SF-6D will be derived from a selection of SF-36 items which will be completed at baseline and follow-up visits during the trial. Any patient who completes the SF-36 can be uniquely classified according to the SF-6D.

Data regarding resource utilisation will be collected via patient notes and patient questionnaire returned at 3, 6 and 12 months along with the other measures of clinical outcome. A range of costs will be considered including the number of physiotherapy sessions attended, medications (including steroid injections) and referrals to surgery (with associated follow-up). These and other unit costs will be taken from the most recent National Reference Costs, British National Formulary and PSSRU publication ‘Unit costs of health and social care’. This will enable an estimation of the total cost for each participant as well as the average total cost for each treatment group.

As with the clinical outcomes, economic analysis will be on an intention-to-treat basis. The between groups differences will be compared using 2-independent samples t-tests. The QALY value will be estimated using straight line interpolation between data points. So, for example, if a patient reports quality of life (QoL) equal to 1 at each time point during the trial this will equate to a QALY of 1 and if they report QoL equal to 0.5 at each time point during the trial this will equate to a QALY of 0.5. Mean incremental costs and QALYs will be combined into an incremental cost effectiveness ratio (ICER) to enable assessment of the relative cost-utility. Sampling uncertainty will be represented by plots on the cost-effectiveness plane and associated cost-effectiveness acceptability curves (CEACs). To reflect uncertainty and to enable valid inferences to be made, any missing data will be imputed using multiple imputation. This process will enable a decision about the acceptability of the intervention in terms of an effective use of NHS resources.

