### Baseline/outcome assessment

After the participants have been assessed for eligibility and consent has been gained, prior to randomisation, they will complete a range of appropriate patient-reported outcome measures to establish baseline pain, function, quality of life and level of self-efficacy. Additionally, the participants’ preference for one treatment or the other, if they had a free choice, will be noted to enable analysis of the effect of preference on outcome.

The primary aim of the proposed study is to evaluate the clinical and cost-effectiveness of self-managed loaded exercise versus usual physiotherapy for rotator cuff disorders. The primary outcome measure will be the Shoulder Pain & Disability Index (SPADI) [24] score at 12 weeks. SPADI is a self-report measure specifically developed to evaluate pain and function in patients with shoulder pathology [25]. It is a commonly used measure which has been validated for use in this patient population and a minimally clinically important change of 10 points has been identified [25]. The SPADI includes 13 items divided into 2 sub-scales; pain (5 items), disability (8 items). The responses are indicated on a visual analogue scale where 0 = no pain/no difficulty and 10 = worst imaginable pain/so difficult it requires help. The items are summed and converted to a total score out of 100.

The Short-form 36 (SF-36) is a generic measure of health related quality of life [26] and is the most widely used measure of this nature. The SPADI & SF-36 will be repeated at 12, 24 and 52 weeks and returned by post. These measures will be complemented by the patient specific functional scale (PSFS) which is a patient-specific outcome measure which investigates functional status and is intended to complement the findings of generic or condition-specific measures [27]. The PSFS has been shown to be valid and responsive in various musculoskeletal populations [28]. Due to the nature of the PSFS, this measure will be completed at baseline and then completed, until the end of the treatment episode, in the presence of the attending physiotherapist. Treatment duration is likely to be in the region of 3 months with the PSFS being completed at 1, 2 and 3 months post baseline.

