### Data analysis

As the trial is a pragmatic parallel group RCT data will be reported and presented according to the revised CONSORT statement and statistical analyses will be performed on an intention-to-treat basis. All statistical exploratory tests will be two-tailed with α = 0.05. Baseline demographic and health-related quality of life data (SF-36) will be assessed for comparability between the treatment groups. The primary aim is to compare the effect of loaded exercise versus usual physiotherapy. The mean SPADI total score at 12 weeks follow-up is the primary efficacy response variable. A two independent samples t-test will be used to compare mean SPADI total scores between the groups (loaded exercise and usual physiotherapy groups). In the event of differences between the groups with respect to baseline measurements, multiple regression or analysis of covariance (ANCOVA) will be used to adjust the treatment effect for these variables. Secondary outcomes will be analysed in a similar way. For the repeated PSFS assessments at baseline and termination of treatment and (SPADI, SF-36) assessments at baseline, 12, 24 and 52 weeks a summary measure such as the Area Under the Curve (AUC) will be calculated for each patient. A two independent samples t-test will be used to compare mean AUC between the groups (loaded exercise and usual physiotherapy groups).

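### Incremental QALYs are compared by an unadjusted t-test although baseline SF-6D is part of every QALY, so chance baseline imbalance carries into the ICER and CEAC

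*Protocol article*

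**What the plan says.** All sections cited are in the protocol article.

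- **Utility source (Economic analysis).** "The SF-6D will be derived from a selection of SF-36 items which will be completed at baseline and follow-up visits during the trial".
- **Timing (Baseline/outcome assessment).** Participants complete the outcome measures before randomisation, and "The SPADI & SF-36 will be repeated at 12, 24 and 52 weeks and returned by post".
- **QALY construction (Economic analysis).** "The QALY value will be estimated using straight line interpolation between data points". The worked example in that section counts utility at every time point.
- **Comparison (Economic analysis).** "The between groups differences will be compared using 2-independent samples t-tests". No covariate is mentioned.
- **Use of the result (Economic analysis).** The mean increments in cost and QALYs form the ICER, and "Sampling uncertainty will be represented by plots on the cost-effectiveness plane and associated cost-effectiveness acceptability curves (CEACs"). The section says this will support a decision about the use of NHS resources.
- **Adjustment rule for clinical outcomes (Data analysis).** "In the event of differences between the groups with respect to baseline measurements, multiple regression or analysis of covariance (ANCOVA) will be used". The section then extends this beyond the primary outcome: "Secondary outcomes will be analysed in a similar way". QALYs and costs are not named there. The only feature that the Economic analysis section takes over from the clinical analysis is the intention-to-treat basis.

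**The concern.** A QALY formed by interpolation from baseline contains the baseline utility. If one arm happens to start with better SF-6D scores, it gains QALYs in two ways: through the first segment of the area under the curve, and because people who start higher tend to stay higher. Treatment produces neither gain. A two-sample t-test on the raw QALYs leaves both in the incremental QALY.

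That increment is the denominator of the ICER and one axis of the cost-effectiveness plane, and it helps to determine the CEAC. Where the true QALY difference is small, a shift of this kind can change the ICER materially or reverse its sign. The Baseline/outcome assessment section places cost-effectiveness within the primary aim, so this is not a minor output.

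**Working it through.** **Inputs from the protocol.** SF-36 at 0, 12, 24 and 52 weeks; linear interpolation; 105 recruited per group (Sample size calculation). The protocol gives no sample size or precision for QALYs, so there is no QALY figure to reproduce. The stated SPADI sample size does reproduce: a 10-point difference, SD 24, 80% power and two-sided 5% give 91 per group, and 91 × 1.15 = 104.65, rounded to 105.

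**Assumed inputs.** SF-6D SD of 0.10 to 0.15, equal at each visit, and a common between-visit correlation r of 0.5 to 0.7. The protocol states neither.

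**Step 1: weight of each visit.** The intervals are 12, 12 and 28 weeks, and each visit takes half of each adjoining interval, divided by 52.

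| Week | Weight |
|---|---|
| 0 | 6/52 = 0.115 |
| 12 | 12/52 = 0.231 |
| 24 | 20/52 = 0.385 |
| 52 | 14/52 = 0.269 |

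On the 3, 6 and 12 month labels used elsewhere in the article, the baseline weight is 0.125, so little changes.

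**Step 2: pass-through of baseline imbalance.** The slope of QALY on baseline SF-6D is 0.115 + 0.885r.

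**Step 3: QALY variance relative to SF-6D variance.** The squared weights sum to (36 + 144 + 400 + 196)/2704 = 0.287, so the ratio is 0.287 + 0.713r.

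**Step 4: share of QALY variance left after adjustment.** This is 1 − slope²/ratio. The standard error falls by 1 − √(share left).

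| r | Slope | Variance ratio | Share left | Fall in SE |
|---|---|---|---|---|
| 0.5 | 0.56 | 0.64 | 0.52 | 28% |
| 0.6 | 0.65 | 0.71 | 0.42 | 36% |
| 0.7 | 0.73 | 0.79 | 0.31 | 44% |

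**Step 5: size of a typical imbalance.** The standard error of the baseline difference is SD × √(2/105) = SD × 0.138, which is 0.014 at SD 0.10 and 0.021 at SD 0.15.

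**Step 6: shift in the incremental QALY from a one-standard-error imbalance.**

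- Low end: 0.0138 × 0.56 = 0.008.
- High end: 0.0207 × 0.73 = 0.015.

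Relative to the unadjusted standard error of the incremental QALY, the shift is slope/√ratio, which is 0.70 at r = 0.5 and 0.83 at r = 0.7. This does not depend on the SD or on the number per arm.

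**Step 7: wider range.** With r from 0.4 to 0.8, the slope runs from 0.47 to 0.82 and the shift from 0.0065 (SD 0.10) to 0.017 (SD 0.15).

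**Step 8: decaying correlation.** Take correlations of baseline with 12, 24 and 52 weeks of 0.5, 0.4 and 0.3, and of 0.6 to 0.7 between follow-ups. The slope is 0.115 + 0.231 × 0.5 + 0.385 × 0.4 + 0.269 × 0.3 = 0.47. About 70% of the variance is left, and the standard error falls by about 17%.

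**The case against.** Four points can be made for the plan.

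1. **Randomisation makes the unadjusted difference unbiased, and its standard error already includes chance imbalance.** This is correct: the t-test is valid inference. What remains is error conditional on the imbalance that occurs, and precision given up for nothing.

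2. **The Data analysis section already provides for adjustment when baseline measurements differ, and SF-36 is among the baseline data to be compared.** A reader could extend that rule to QALYs. But it names only secondary outcomes, while the Economic analysis section states its own test. The Data analysis section also gives a plain t-test for the clinical areas under the curve, which have the same structure as a QALY. Even if the rule were extended, it has no stated trigger, and adjustment that depends on the observed imbalance is weaker than a covariate fixed in advance.

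3. **The t-test sentence does not name QALYs, and the article does not say how the increments behind the ICER and CEAC are estimated.** True as to wording. Costs and QALYs are, however, the only quantities compared in that section, and the natural reading of a mean increment beside a t-test is the raw difference in means. A health-economics plan could say otherwise; the article does not.

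4. **The size rests on assumed figures.** This stands. The direct baseline weight is small, most of the pass-through comes from the assumed correlations, and decaying correlations reduce the gain. No cost or willingness-to-pay figures are given, so no reversal of the decision is shown. The trial's power for SPADI at 12 weeks is unaffected.

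**Conclusion.** The concern holds. The article names an unadjusted test for an outcome that contains its own baseline, so this is a stated choice and not a detail left open. With SF-6D SD 0.10 to 0.15, equal correlations of 0.5 to 0.7 and 105 per arm, an ordinary chance imbalance shifts the incremental QALY by about 0.008 to 0.015, or 0.70 to 0.83 of its unadjusted standard error. Adjustment would cut that standard error by 28 to 44%, or by about 17% in the decaying-correlation example. The size depends on these assumptions. The direction needs only a positive relation between baseline and later utility. The change should be made, but the unadjusted analysis is inefficient rather than invalid.

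**What to change.** In the SAP or health-economics plan, replace the t-test for QALYs with a regression of QALY on treatment group and baseline SF-6D, specified in advance and applied whether or not imbalance is seen. Fit the same model within each multiply imputed data set and in whatever procedure generates the cost-effectiveness plane and CEAC, so that the ICER and its uncertainty rest on the adjusted increment. Report the unadjusted difference as a sensitivity analysis.

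The cost is a few sentences of plan wording. Baseline SF-36 is already collected, so no new data, visits or participants are needed.

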### The qualitative investigation

The primary objective of the qualitative investigation is to explore perceptions and experience of the study participants. The intervention is largely self-managed and can be uncomfortable for patients which is in contrast to the majority view of usual physiotherapy [22]. Hence this aspect of the study is important to provide complementary data to the findings of the RCT because these factors might serve as barriers to successful outcome and/or real world implementation.

### Recruitment

Participants for the qualitative aspect of the study will be purposively selected from the treating physiotherapists and those patients recruited to the intervention arm of the RCT. All patient participants randomised to the intervention arm of the RCT will be eligible to enter and will be selected to gain a balanced sample of male/female and treatment adherers/non-adherers. All therapists involved in the delivery of the intervention will be eligible to enter.

Information relating to this aspect of the study will be included in the initial participant information sheet. The chief investigator (CL) will identify potential patient participants from the data generated by the RCT and will initially contact them by telephone to discuss whether they would be able to discuss their experiences. If their response is favourable then a separate consent form will be posted to them and completed prior to being invited to attend an individual interview at their convenience. The interviews may be conducted at the patients’ home or physiotherapy department.

The eligible physiotherapists will be approached as a group during the regular training sessions held throughout the duration of the trial, led by the chief investigator, and an open letter including a participant information sheet and consent form will invite them to contact CL with a view to discussing participation in this aspect of the study. If the physiotherapist wishes to participate then a mutually convenient individual interview at the physiotherapy department will be scheduled.

It is expected that interviews will last between 30 to 60 minutes. Purposive sampling will continue until data saturation. Data saturation is the point where on-going analysis reveals no new themes emerging from the data but it is estimated that 10 to 20 patient interviews will be required and up to 10 therapist interviews. Once it is thought that data saturation has been attained, 2 more interviews will be conducted to confirm this.

### Data collection

Interviews will be directed by topic guides These discussions will be recorded using a digital voice recorder and subsequently transcribed verbatim.

### Data analysis

CL and SM will analyse the data using the framework approach.

The framework approach has been developed specifically for applied research in which the objectives of the investigation are set *a* priori [33]. The 5 stages of data analysis associated with the framework approach are as follows:

1. Familiarisation – identifying key ideas and themes

2. Identifying a thematic framework – identifying all key issues, concepts and themes by which the data can be examined

3. Indexing – application of the thematic framework to all the data

4. Charting – Organisation of the data according to the defined thematic framework to which they relate to form common charts

5. Mapping and Interpretation – using the charts to define concepts, map the range and nature of phenomena, create typologies and find associations with a view to providing explanations for the findings.

One clear advantage of the framework method is the systematic and visible stages of the analysis process [34,35]. The patients and physiotherapists involved will be invited to inspect the outcomes of the analysis in an attempt to maximise validity of the interpretations.

### Patient & public involvement

A formal patient and public involvement event was held with the aim of seeking lay opinion regarding the design and conduct of the SELF study. A focus group led by CL and JA was undertaken with a sample of volunteers currently attending for physiotherapy at Doncaster & Bassetlaw Hospitals NHS Foundation Trust. In summary, the lay group found our initial proposals acceptable but suggested that initial approach by letter, a full description of the content of the treatment arms, an enhanced exercise diary incorporating a visual illustration of any prescribed exercise and encouragement to the physiotherapists involved to help set specific treatment goals might improve the design and conduct of the SELF study. These features have been incorporated into this current version of the protocol.

## Ethical approval

The protocol was approved by the National Research Ethics Service Committee Yorkshire & the Humber – Leeds West, UK on the 6^th^ January 2012.
